## Abstract

Supporting Carers of Children and Adolescents with Eating Disorders in Austria (SUCCEAT) is an intervention for carers of children and adolescents with anorexia nervosa and atypical anorexia nervosa. This paper describes the study protocol for a randomised controlled trial including the process and economic evaluation. Carers are randomly allocated to one of the 2 SUCCEAT intervention formats, either 8 weekly 2‐hr workshop sessions (*n* = 48) or web‐based modules (*n* = 48), and compared with a nonrandomised control group (*n* = 48). SUCCEAT includes the cognitive‐interpersonal model, cognitive behavioural elements, and motivational interviewing. The goal is to provide support for carers to improve their own well‐being and to support their children. Outcome measures include carers' distress, anxiety, depression, expressed emotions, needs, motivation to change, experiences of caregiving, and skills. Further outcome measures are the patients' eating disorder symptoms, emotional problems, behavioural problems, quality of life, motivation to change, and perceived expressed emotions. These are measured before and after the intervention, and 1‐year follow‐up.

## INTRODUCTION

1

Anorexia nervosa (AN) is a severe mental disorder with high mortality rates compared with other mental disorders (standardised mortality ratio = 5.9, 95% CI [4.2, 8.3]; Chesney, Goodwin, & Fazel, 2014). It is state of the art to involve carers (mostly parents) in the treatment of children and adolescents with eating disorders (EDs; National Institute for Clinical Excellence [NICE], 2017). Caring for a child who suffers from AN can have a serious emotional impact on the parents and lead to distress, anxiety, and depression (Kyriacou, Treasure, & Schmidt, 2008b; Whitney, Haigh, Weinman, & Treasure, 2007; Zabala, Macdonald, & Treasure, 2009).

On the one hand, previous studies have revealed that some parents are likely to show unhelpful behaviours for the patients' outcome, such as accommodating behaviours and dysfunctional interpersonal interactions. It is mostly the mothers of adolescent patients who spend more time involved in care compared with fathers, mainly providing food and emotional support; and they usually report higher levels of distress and accommodating behaviour (Rhind et al., 2016). Family members tend to show accommodating behaviours and reorganise their behaviours around the ED symptoms: For example, they accept meal rituals and low‐calorie foods and turn a blind eye to unwanted behaviours (Sepulveda, Kyriacou, & Treasure, 2009). When both parents are highly accommodating, these accommodating behaviours may maintain the illness and negatively influence the outcome of adolescents (Salerno, Rhind, Hibbs, Micali, Schmidt, Gowers, Macdonald, Goddard, Todd, Lo Coco, et al., 2016a). When the families' level of stress increases, family members are at risk of developing high expressed emotions (HEE; i.e., criticism and emotional overinvolvement; Sepulveda et al., 2010). Anxious parents, for example, might show emotional overinvolvement, which potentially prevents the patients' independence and inhibits their sense of self‐efficacy (Kyriacou, Treasure, & Schmidt, 2008a; Whitney et al., 2005).

On the other hand, there are families who seek help with their caregiving role (Haigh & Treasure, 2003; Zitarosa, de Zwaan, Pfeffer, & Graap, 2012). The importance of supportive interventions for the caregivers of someone with an ED has been demonstrated in various studies (Magill et al., 2016; Schwarte et al., 2017; Spettigue et al., 2015; Treasure et al., 2001). Family therapy has been proven to be effective with adolescent ED patients (Ciao, Accurso, Fitzsimmons‐Craft, Lock, & Le Grange, 2015; Eisler et al., 2016). Strategies to meet the needs of parents of patients with EDs aim to equip parents with knowledge and behaviour change skills. There are different approaches described in the literature: workshops for families (Whitney, Murphy, et al., 2012; Treasure, Whitaker, Todd, & Whitney, 2012), self‐care interventions with the guidance of experienced and trained carers including DVDs (Experienced Carers Helping Others, ECHO; Goddard, Macdonald, Sepulveda, et al., 2011; Goddard, Hibbs, et al., 2013; Goddard, Raenker, et al., 2013; Hibbs, Magill, et al., 2015; Magill et al., 2016), and intervention via the Internet (Grover, Naumann, et al., 2011; Grover, Williams, et al., 2011; Hoyle, Slater, Williams, Schmidt, & Wade, 2013). All of these approaches rely on “The New Maudsley Method” (Treasure, Schmidt, & Macdonald, 2010; Treasure, Smith, & Crane, 2007). The “New Maudsley Method” was developed for the adult carers of adult patients, and little work in this area has been carried out with the carers of adolescent patients. The ‘”New Maudsley Method” was found to reduce carers' HEE (emotional overinvolvement and criticism), distress, burden (Hibbs, Rhind, Leppanen, & Treasure, 2015), anxiety, negative experiences of caregiving (Grover, Naumann, et al., 2011), and time spent caregiving (Hibbs, Magill, et al., 2015). It was shown that the parents' improvement had positive effects on the patients with ED themselves. These included reduction of the ED psychopathology of patients with AN, a reduction of their inpatient bed days (Hibbs, Magill, et al., 2015), an improvement in their quality of life, and an increase in their weight gain (Goddard, Hibbs, et al., 2013; Whitney, Murphy, et al., 2012). Adult patients showed a positive attitude to involving parents in their care (Goddard, Macdonald, & Treasure, 2011).

The previous studies mostly included adult patients and fewer or no adolescent patients. Only one randomised controlled trial (RCT) has examined the effects of the self‐help intervention ECHO for parents of adolescent patients exclusively (13–21 years) so far (Rhind et al., 2014). Parents of adolescents received the training materials (a book and a set of DVDs), and coaches (individuals with experience in caregiving for someone with an ED) provided guidance via telephone. The parents of adolescents rated the intervention favourably and reported positive experiences on account of the ECHO intervention (Goodier et al., 2014). Optimising caregiving skills and reducing accommodating behaviours by the carers could aid the recovery of the patients (Salerno, Rhind, Hibbs, Micali, Schmidt, Gowers, Macdonald, Goddard, Todd, Lo Coco, et al., 2016a; Salerno, Rhind, Hibbs, Micali, Schmidt, Gowers, Macdonald, Goddard, Todd, Tchanturia, et al., 2016b).

A recent meta‐analysis of interventions for parents of children with EDs highlights a clear need for RCTs that include outcomes for the children and adolescents (Hibbs, Rhind, Leppanen, et al., 2015). In addition, there is also a need to make interventions for parents cost‐effective (Roick et al., 2001), available, and affordable (Fairburn & Patel, 2014).

Supporting Carers of Children and Adolescents with Eating Disorders in Austria (SUCCEAT) is based on “The New Maudsley Method” (MacDonald, Todd, Whitaker, Creasy, Langley, & Treasure, in prep.; Schmidt & Treasure, 2006; Treasure et al., 2010; Treasure, Smith, et al., 2007). For the SUCCEAT intervention, the material from “The New Maudsley Method” was adapted as a therapeutic 8‐week intervention for use with carers of children and adolescents (see Table 1). These were translated into German and also adapted to a German‐speaking cultural context (Treasure et al., in prep.). This is the first protocol for an RCT, which compares workshop support groups with web‐based support groups directly and also includes outcome of patients younger than 13 years (10–19 years).

**Table 1 erv2600-tbl-0001:** SUCCEAT intervention components based on the cognitive‐interpersonal maintenance model^a^

Content of eight SUCCEAT workshops sessions and web‐based modules		Aims
Interpersonal Factors	Aetiology of anorexia nervosa; explanation of relationship patterns: high expressed emotions, caring styles, and animal models	Knowledge about the illness, caring with just enough control, compassion, and consistency
Brain and Compassion	Effects of anorexia nervosa on the brain, thinking styles, obsessive‐compulsive personality traits, and self‐compassion	Recognising one's own thinking styles and personality traits, increasing flexibility, and being self‐compassionate
Stages of Change	Transtheoretical Model of change (Prochaska & DiClemente, 1984), eliciting confidence, importance, and readiness to change	Recognizing the different stages of change and supporting changes in these different stages
Motivational Interviewing I	Introduction to Motivational Interviewing (Miller & Rollnick, 2002), main principles of reflective listening and communication	Expressing empathy, motivating change, rolling with resistance, and supporting self‐efficacy
Motivational Interviewing II	Enhancement of Motivational Interviewing, communication tools: reflection, reframing, etc.	Initiating change talk (refers to desire, ability, reasons, and needs to change) and avoiding communication traps
Stress and Emotions	Improving emotional intelligence and managing personality traits (perfectionism and avoidance)	Supporting emotional self‐regulation
Difficult Behaviours	Coping with difficult behaviours, elements of cognitive behavioural therapy: Antecedent–Behaviour–Consequence (ABC model; Ellis, 1973)	Changing antecedents, behaviours, and consequences
Stage of Maintenance	Recognising recovery, complete remission, and partial remission; crisis management	Preventing relapses
Additional material offered to the carers		
DVD^b^	Instructions explain communication skills and animal models Role play scenarios show examples for disadvantageous and advantageous communication Audio files give examples of providing meal support	
SUCCEAT workbook	Summarises and extends the contents of the intervention, and contains further information and exercises One chapter informs the patients about the intervention	

*Note*. SUCCEAT = Supporting Carers of Children and Adolescents with Eating Disorders in Austria.

a MacDonald, Todd, Whitaker, Creasy, Langley & Treasure, in prep.; Treasure et al. (2010); Treasure, Smith, et al. (2007); Schmidt and Treasure (2006); and Treasure and Schmidt (2013).

b
*How to Care for Someone with an Eating Disorder* (The Succeed Foundation, 2011; German translation of our research group).

### Theoretical background of the SUCCEAT intervention

1.1

The SUCCEAT intervention highlights several benefits of “The New Maudsley Method” (Treasure, Smith, et al., 2007; Treasure et al., 2010; Treasure & Nazar, 2016). “The New Maudsley Method” consists of psychoeducation (e.g., aetiology of EDs, the effects of starvation on the brain, emotional self‐regulation, and personality traits) and communication tools; and it incorporates different theoretical models:
Motivational Interviewing (MI; Miller & Rollnick, 2002),the cognitive‐interpersonal maintenance model (Goddard, Salerno, et al., 2013; Schmidt & Treasure, 2006; Treasure & Schmidt, 2013),the Antecedent–Behaviour–Consequence model (ABC model; Ellis, 1973), andthe Transtheoretical Model of Change (Prochaska & DiClemente, 1984).

Besides the focus on MI in two workshop sessions and web‐based modules, respectively (see Table 1), the whole SUCCEAT intervention provides skills for behaviour change through an MI framework (Miller & Rollnick, 2002; Treasure et al., 2012). The coaches from the SUCCEAT intervention act as role models and use MI to enable the parents to be self‐compassionate and to care for themselves (Schulz von Thun, 1981; Sepulveda, Lopez, Todd, Whitaker, & Treasure, 2008). The parents learn how to apply MI: to express empathy, to motivate change through discrepancy, to roll with resistance, and to support self‐efficacy (Sepulveda, Lopez, Macdonald, & Treasure, 2008).

The SUCCEAT intervention is based upon the cognitive‐interpersonal maintenance model of AN (Schmidt & Treasure, 2006; Treasure & Schmidt, 2013). This model proposes that the following factors cause and maintain EDs: (1.) obsessive–compulsive personality traits, (2.) avoidance as a personality characteristic, (3.) positive beliefs about the illness, and (4.) responses of close others.
Obsessive–compulsive personality traits, such as perfectionism and rigidity in patients with AN, can lead to attention to details and a fear of making mistakes, which may cause the illness to be maintained (Crane, Roberts, & Treasure, 2007; Swinbourne et al., 2012; Treasure et al., 2008).Patients with AN tend to avoid experiences, intense emotions, and close relationships (Krug et al., 2012; Russell, Schmidt, Doherty, Young, & Tchanturia, 2009; Zabala et al., 2009). As a result of the loss of brain power, starvation may increase avoidance and rigidity (Anderluh, Tchanturia, Rabe‐Hesketh, & Treasure, 2003; Cardi et al., 2017; Cardi, Di Matteo, Corfield, & Treasure, 2012; Davies, Schmidt, Stahl, & Tchanturia, 2011; Sternheim et al., 2012; Treasure & Russell, 2011; Treasure, Sepulveda, et al., 2007). Some parents share obsessive–compulsive and avoidant personality traits (Fassino et al., 2002; Treasure et al., 2008; Treasure & Cardi, 2017; Ward et al., 2001). As parents often serve as a role model for their children, SUCCEAT teaches the parents how to show flexible behaviour (Harrison, Tchanturia, Naumann, & Treasure, 2012; Roberts, Tchanturia, Stahl, Southgate, & Treasure, 2007), to pay less attention to details (Goddard, Raenker, et al., 2013), and to overcome the fear of making mistakes (Goddard, Raenker, et al., 2013; Kanakam, Raoult, Collier, & Treasure, 2012).Many patients with AN have positive beliefs about their illness. The patients believe that the illness helps them to feel in control, to feel special and powerful, to cope with emotions, and to have a sense of autonomy (Branch & Eurman, 1980; Serpell, Teasdale, Troop, & Treasure, 2004). To address these positive beliefs, parents are equipped with skills to help their children to reach these positive feelings (control, autonomy, etc.) by other means than the ED (Treasure, 2016b).Several distressing ED symptoms make the parents anxious (Treasure et al., 2008). Parents sometimes try to reduce their anxiety by using HEE. Animal metaphors are used to reflect dysfunctional interaction styles (Sepulveda, Lopez, Macdonald, et al., 2008). SUCCEAT emphasises the importance of collaborative caregiving. Parents are equipped with health promoting skills, function as partners of the professionals, and work like cotherapists towards patients' recovery (Macdonald, Murray, Goddard, & Treasure, 2011; Sepulveda, Lopez, Todd, et al., 2008). Carers are taught how to give just enough guidance and to care for the patient with warmth, compassion, and consistency (Gilbert, 2009).

Some ED behaviours of the patients have become automated habits (e.g., over‐exercising, vomiting, and fasting) and are no longer related to goals (Nazar et al., 2017), and some patients use the ED behaviours to deal with stressful situations (Treasure et al., 2008). One strategy to change difficult behaviours is the ABC model (Ellis, 1973). The ABC model from cognitive behavioural therapy enables the parents to help the patients change their difficult behaviours by changing antecedents (e.g., creating a comfortable atmosphere before dinner), changing their own behaviour (e.g., talking about pleasant themes during dinner), and consequences (e.g., going for a walk together after dinner). Another strategy to change difficult behaviours is changing it according to the Transtheoretical Model of Change (Prochaska & DiClemente, 1984). Carers are trained to identify which stage of change they are in themselves and which stage the patient is in (Treasure, 2016a; Whitney, Currin, Murray, & Treasure, 2012). Parents are taught how to support change in the different stages (Treasure, Sepulveda, et al., 2007). The SUCCEAT intervention informs the parents that patients sometimes relapse and need to go through repeated cycles of the stages of change (Hibbs, Magill, et al., 2015; McKnight & Boughton, 2009; Taborelli et al., 2016). The different theoretical models combine intrapersonal and interpersonal factors, as well as knowledge and skills, that can help parents to manage their own reaction to the illness and to provide an environment that is conducive to change (Treasure et al., 2010).

### The SUCCEAT trial aims

1.2

There are three main goals of the SUCCEAT intervention: first, to increase the well‐being of the carers in order to reduce their own risk of developing a mental disorder; second, to support children's and adolescents' recovery from EDs; and third, to attain long‐term changes in the communication within the families to prevent patients from relapsing. A long‐term goal is to provide low‐threshold, cost‐effective, time‐efficient, and transregional support for carers in the future.

### Hypotheses

1.3

The outcome measures are mentioned in brackets. These outcome measures are described in more detail in Table 2 and in Supplement S1.

**Table 2 erv2600-tbl-0002:** Outcome measures of the RCT

Instrument	Abbrev.	Domain	Purpose
General Health Questionnaire (Linden et al., 1996)	GHQ	Psychological morbidity and distress^a^	PO, C
Eating Disorder Examination (Hilbert & Tuschen‐Caffier, 2006)	EDE	ED symptomatology^b^	PO, P
Eating Disorder Inventory‐2 (Paul & Thiel, 2005)	EDI‐2	Various dimensions of EDs^a^	PO, P
Caregiver Skills (Hibbs, Rhind, Salerno, et al., 2015, c)	CASK	Skills to support a child with an ED^a^	SO, C
Experience of Caregiving Inventory (Szmukler et al., 1996, c)	ECI	Experiences in caring^a^	SO, C
Eating Disorder Symptom Impact Scale (Sepulveda, Whitney, Hankins, & Treasure, 2008, c)	EDSIS	Burden concerning caring for a child with an ED^a^	SO, C
Carers' Needs Assessment Measure (Graap et al., 2005)	CaNAM	Unmet needs respective caring^a^	SO, C
Symptom Checklist 90 (Franke, 2002)	SCL‐90	Psychiatric symptomatology^a^	SO, C
Beck Depression Inventory‐II (Hautzinger, Keller, & Kühner, 2006)	BDI‐II	Depressive symptomatology^a^	SO, C
State‐Trait‐Anxiety Inventory (Laux, Glanzmann, Schaffner, & Spielberger, 1981)	STAI	State and trait anxiety^a^	SO, C
Family Questionnaire (Wiedemann, Rayki, Feinstein, & Hahlweg, 2002)	FQ	High expressed emotions^a^	SO, C
University of Rhode Island Change Assessment Scale (Hasler, Klanghofer, & Buddeberg, 2003)	FEVER	Readiness for change^a^	SO, C
Body Mass Index (clinical measures of height and weight)	BMI	Weight status^a^	SO, P
Youth Self‐Report (Arbeitsgruppe Deutsche Child Behavior Checklist, 1998)	YSR	Behavioural, emotional problems^a^	SO, P
Health‐Related Quality of Life Questionnaire for Children and Adolescents (Ravens‐Sieberer & Bullinger, 1998a, 1998b)	KINDL	Quality of life^a^	SO, P
Family Emotional Involvement and Criticism Scale (Kronmüller et al., 2001)	FEIWK	Perceived HEE^a^	SO, P
Anorexia Nervosa Stages of Change Questionnaire (Rieger, Touyz, & Beumont, 2002, c)	ANSOCQ	Readiness to recover from AN^a^	SO, P
SUCCEAT Treatment Satisfaction Questionnaire		Feasibility and acceptability of the SUCCEAT intervention	C, Process evaluation
Client Sociodemographic and Service Receipt Inventory (Roick et al., 2001)	CSSRI	Cost‐effectiveness	C, P Economic evaluation

*Note*. SUCCEAT = Supporting Carers of Children and Adolescents with Eating Disorders in Austria; RCT = randomised controlled trial; HEE = high expressed emotions; AN = anorexia nervosa; PO = primary outcome; SO = secondary outcome; C = carers' assessment; P = patients' assessment; ED = eating disorder;

a Self‐report measure.

b Semistructured interview.

c German translation of our research group with back translations by an English native‐speaking psychologist.

#### Primary hypothesis—Carers

1.3.1

Carers participating in the SUCCEAT intervention groups will report a greater reduction of distress (General Health Questionnaire: Linden et al., 1996) at postintervention (T1) than the carers in the control group.

#### Primary hypothesis—Patients

1.3.2

Patients whose carers participate in the SUCCEAT intervention groups will show a greater reduction of ED symptoms (Eating Disorder Examination: Hilbert & Tuschen‐Caffier, 2006; Eating Disorder Inventory 2: Paul & Thiel, 2005) at postintervention (T1) than the patients in the control group.

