### Sample size calculations

2.5

Power analysis was done with G*Power version 3.1.5. In order to detect a difference for the primary outcome (General Health Questionnaire, see Sepulveda, Lopez, Todd, et al., 2008) by calculating repeated measures analysis of variance (ANOVA; if the s*phericity* assumption is not met) at a 5% significance level with 0.88 power, carers of 40 patients per group are needed to detect medium effects (Faul, Erdfelder, Lang, & Buchner, 2007). We expect a dropout rate of about 17% (see Wagner et al., 2015). Therefore, we plan to include the carers of 48 patients per treatment arm, resulting in a total sample size of 144.

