### Statistical analysis plan

2.8

The treatment effect will be analysed by using mixed‐design ANOVAs. The time points will be included as within group factor, and the group (workshop support group vs. web‐based support group vs. TAU) will be included as between group factor. *t* tests for dependent and independent samples will also be used in order to explore differences between specific groups and specific time points.

Two analysis strategies will be applied to account for missing data: Intention‐to‐treat analysis will be used as the primary analysis strategy. If posttreatment or follow‐up data are missing, the last‐value‐put‐forward method will be used. Additionally, the analyses will be repeated by including completers only. Completers will be defined by attending more than 50% of the workshop sessions or web‐based modules. To analyse the potential effect of treatment moderators, additional ANOVAs will be calculated including patient's age and duration of illness as covariates.

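### The protocol names three primary outcomes under two primary hypotheses but sizes the trial for one, and gives no rule for combining or ordering them, so a trial-wide 5% error rate is not secured

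*Protocol article*

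**What the plan says.** - **Number of primary outcomes.** Table 2 (section 1.3) gives the primary-outcome label to the GHQ, EDE and EDI-2, and the table note defines that label.
- **Hypotheses.** Section 1.3.1 is a primary hypothesis for carers on the GHQ at T1. Section 1.3.2 is a second primary hypothesis, for patients at T1: they "will show a greater reduction of ED symptoms". EDE and EDI-2 stand in one bracket after it, with no and, no or, and no ranking.
- **Sample size.** Section 2.5 begins "In order to detect a difference for the primary outcome (General Health Questionnaire" and continues "at a 5% significance level with 0.88 power, carers of 40 patients per group are needed to detect medium effects". EDE and EDI-2 are not mentioned there.
- **Analysis.** Section 2.8 fixes mixed-design ANOVAs, the handling of missing data, a completer analysis and two covariates, and adds that t "tests for dependent and independent samples will also be used in order to explore differences between specific groups and specific time points". It states no significance level, testing order, alpha split or success rule. The only significance level in the article is the 5% in section 2.5.

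**The concern.** Sections 1.3 and 2.5 cannot both stand: the trial has either one primary outcome or three. The difference matters because the 5% and the 0.88 power belong to a design with one primary test. With three primary outcomes and no stated rule, a primary success could be claimed on whichever instrument turns out favourably.

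Section 1.3.2 has the same gap on a smaller scale. If the EDE improves more than in controls and the EDI-2 does not, the text does not say whether the patient hypothesis is met. That choice could then be made after the data are seen.

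**Working it through.** **1. Reproduce the plan's own figure.** Inputs from section 2.5: alpha 0.05, power 0.88, 40 per group. Section 2.8 gives three groups and section 2.8 with section 2.4 three time points. Assumption: a medium effect means f(V) = 0.25, since the article gives only the word.

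The group-by-time test is taken in its multivariate repeated-measures form, which fits the section's remark about sphericity:
- N = 3 × 40 = 120 and s = min(3 − 1, 3 − 1) = 2
- noncentrality = N × s × f² = 120 × 2 × 0.0625 = 15
- df1 = (3 − 1)(3 − 1) = 4; df2 = 2 × (120 − 3 − 2 + 2) = 234
- power = 0.884

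The smallest balanced N that reaches 0.88 is 120; at N = 117 power is 0.875. The GHQ sample size reproduces and is not in question.

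**2. Three unadjusted tests at 5%, any one sufficing.** If independent: 1 − 0.95³ = 0.143. The upper bound is 3 × 0.05 = 0.15. Correlated cases are simulated with two-sided normal tests. The article gives no correlations, so these are assumptions.

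| EDE with EDI-2 | GHQ with patient outcomes | False primary success |
|---|---|---|
| 0 | 0 | 14.3% |
| 0.5 | 0.2 | 13.4% |
| 0.5 | 0.5 | 12.5% |
| 0.7 | 0.7 | 10.9% |
| 0.9 | 0.5 | 10.8% |

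**3. The patient hypothesis alone, EDE and EDI-2 each at 5%.**
- Either rule: 1 − 0.95² = 9.75% if independent, about 9.1% at correlation 0.5, about 7.0% at 0.9.
- Both rule: at most 5%, because each test must itself reach significance at 5%.

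**4. Both rule for patients, with the carer hypothesis kept separate at 5%.** Each hypothesis is then held at 5% or less. The chance of at least one false claim across the two is at most 5% + 5% = 10%.

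**5. What an adjustment would cost.** Formula from step 1, f(V) = 0.25:

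| Alpha for GHQ | Power at 40 per group | Per group for 0.88 | After 17% dropout |
|---|---|---|---|
| 0.05 | 0.884 | 40 | 48 as planned (40/0.83 = 48.2) |
| 0.05/3 = 0.0167 | 0.777 | 50 | 61 (50/0.83 = 60.2) |

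The second row is the worst case for the GHQ under Holm, which tests at a higher level once another outcome has been rejected. Under a fixed order with the GHQ first, the first row applies unchanged.

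**The case against.** The strongest reply is that the article never claims a trial-wide 5%. Its only 5% belongs to the GHQ power analysis, and section 2.8 sets no level for the other outcomes. The two primary hypotheses concern different people, and whether separate hypotheses need joint control is debated. A success rule or multiplicity procedure may stand in a full protocol or analysis plan that is not shown, and Supplement S1 may name the score for each instrument.

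Much of this stands as a limit on the wording. A reader might infer that each outcome is tested at 5%, that either patient instrument suffices, and that the 5% therefore fails. The text says none of this, and under a both rule the patient hypothesis stays within 5%. Two further inferences are also unsupported:
- The entry "Various dimensions of EDs" in Table 2 describes what the EDI-2 measures. It is not a plan to let any subscale count as success.
- The t tests are described as exploratory, with no level and no list of comparisons. They are not a route to primary success, and the article gives no basis for counting them.

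The conflict between sections 1.3 and 2.5 survives the reply. An unseen document could supply a rule, but these sections would still disagree on the number of primary outcomes.

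**Conclusion.** The point holds as an inconsistency with a conditional consequence. Table 2 and sections 1.3.1 and 1.3.2 name three primary outcomes, section 2.5 names one, and nothing in the article links them, so a trial-wide 5% is not secured. Its size depends on the rule adopted:
- About 11% to 14% if all three are tested unadjusted at 5% and any one suffices.
- About 7% to 10% for the patient hypothesis alone under an either rule, and at most 5% under a both rule.
- No excess if an order, an alpha split or a requirement that all three succeed is set.

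The ranges rest on assumed correlations and two-sided tests. The power figures rest on f(V) = 0.25 and on the test form that reproduces the stated 40 per group. None of this addresses the non-randomised control group, which is a separate matter.

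**What to change.** Align Table 2 and sections 1.3.1, 1.3.2, 2.5 and 2.8 on one confirmatory procedure, fixed before the outcome data are analysed. The preferred form is a fixed order:
1. GHQ first, at 5%.
2. EDE at 5%, only if the GHQ test is significant.
3. EDI-2 at 5%, only if the EDE test is significant.

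Name one score for each instrument and the T1 group comparison that the order applies to. This agrees with section 2.5 and keeps 40 per group and 0.88 power, so it costs only wording. Its downside is that no confirmatory patient claim is possible if the GHQ test fails, however clear the patient results are.

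Holm across the three outcomes avoids that dependence, but its cost must then be stated in section 2.5: worst-case GHQ power falls from 0.88 to about 0.78 at 40 per group. Restoring 0.88 in that case would take 50 per group, or about 61 with the 17% dropout allowance.

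Under either option, report the t tests as exploratory estimates with confidence intervals and base no confirmatory claim on them.
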